## Abstract

**Background:**

Pregnant women at high risk for developing a hypertensive disorder of pregnancy require frequent antenatal assessments, especially of their blood pressure. This expends significant resources for both the patient and healthcare system. An alternative to in-clinic assessments is a remote blood pressure monitoring strategy, in which patients self-record their blood pressure at home using a validated blood pressure machine. This has the potential to be cost-effective, increase patient satisfaction, and reduce outpatient visits, and has had widespread uptake recently given the increased need for remote care during the ongoing COVID-19 pandemic. However robust evidence supporting this approach over a traditional face-to-face approach is lacking, and the impact on maternal and foetal outcomes has not yet been reported. Thus, there is an urgent need to assess the efficacy of remote monitoring in pregnant women at high risk of developing a hypertensive disorder of pregnancy.

**Methods:**

The REMOTE CONTROL trial is a pragmatic, unblinded, randomised controlled trial, which aims to compare remote blood pressure monitoring in high-risk pregnant women with conventional face-to-face clinic monitoring, in a 1:1 allocation ratio. The study will recruit patients across 3 metropolitan Australian teaching hospitals and will evaluate the safety, cost-effectiveness, impact on healthcare utilisation and end-user satisfaction of remote blood pressure monitoring.

**Discussion:**

Remote blood pressure monitoring is garnering interest worldwide and has been increasingly implemented following the COVID-19 pandemic. However, robust data regarding its safety for maternofoetal outcomes is lacking. The REMOTE CONTROL trial is amongst the first randomised controlled trials currently underway, powered to evaluate maternal and foetal outcomes. If proven to be as safe as conventional clinic monitoring, major potential benefits include reducing clinic visits, waiting times, travel costs, and improving delivery of care to vulnerable populations in rural and remote communities.

**Trial registration:**

The trial has been prospectively registered with the Australian and New Zealand Clinical Trials Registry (ACTRN12620001049965p, on October 11th, 2020).

## Background

Hypertensive disorders of pregnancy (HDP), and particularly preeclampsia contribute towards significant short- and long-term maternal morbidity and increase foetal morbidity and mortality 5–sixfold [1]. Women with chronic hypertension, kidney disease, preexisting diabetes mellitus, a previous HDP particularly preeclampsia, and autoimmune disease [2, 3] are considered high risk for developing preeclampsia. A recent study revealed the rate of HDP in this high-risk population was up to 33.8%, with an associated high rate of adverse foetal outcomes (intrauterine growth restriction or preterm delivery) between 15 and 17% [4]. The long-term maternal effects of preeclampsia are also increasingly recognised as a lifetime increased risk of chronic hypertension, coronary artery disease, renal disease and stroke [3, 5–7].

The United Kingdom (UK) National Institute for Health and Care Excellence (NICE) guidelines recommend that women at high risk be identified before week 12 of gestation, commence low-dose aspirin, and undertake more frequent blood pressure (BP) measurements than standard antenatal care [2, 8]. Consequently, this leads to additional outpatient appointments throughout their pregnancy [9], which expends significant resources at the level of both the patient and healthcare system. Frequent monitoring can be a source of anxiety for women and their families, is demanding for patients in terms of time, transport costs and work absence, and has significant service implications for healthcare providers [10].

In recent years, there has been an increasing focus on mobile health (mHealth) technologies, such as mobile phones, patient monitoring devices, and other wireless devices, to make healthcare delivery more efficient [11]. Compared to traditional methods of disease surveillance, mHealth has been found to have improved accuracy, reductions in time and cost, and improved data quality [11]. As such, remote BP monitoring, in which patients monitor and record their own BP using a validated machine, with instructions from a healthcare professional on the frequency of monitoring, has garnered increasing interest [10]. Additionally, the COVID-19 pandemic drastically limited social movement, and therefore initiated widespread uptake of telehealth services to reduce dependence on hospital‐based care, and remote BP monitoring was often required [12].

In the non-pregnant population, remote BP monitoring has been shown to provide a better estimate of underlying BP and long-term outcomes [13, 14]. In the pregnant population, a systematic review of clinical practice guidelines for hypertensive disorders of pregnancy found that most international guidelines recommended remote BP monitoring for hypertension control [15], yet robust evidence for this is lacking.

Studies exploring the use of remote BP monitoring in the antepartum have shown that remote BP monitoring is feasible in pregnant women [16–20], and may even be favourable to conventional clinic monitoring [21–24]. There were less outpatient antenatal visits and day assessment unit attendances [10, 17, 22, 25, 26] when compared to conventional care. There is also a potential beneficial economic impact to the healthcare system, which facilitates the widespread adoption of remote monitoring [27, 28]. No individual study was powered for maternal, foetal and neonatal outcomes as primary outcomes [10, 16, 20, 25–27]. A meta-analysis however found remote BP monitoring was associated with reduced odds of labour induction and prenatal hospital admissions, with no significant differences in foetal outcomes [29]. Similar findings are revealed in postpartum studies, with good feasibility, acceptability [30–34], and fewer hypertension-related hospital admissions [30, 33, 35]. Significant heterogeneity exists amongst these studies [17, 21–23, 36], making applicability of findings difficult. There is also a lack of large antenatal randomised controlled trials with maternal and foetal outcomes as the primary outcome [16, 17, 24].

## Methods

In the “REMOTE blood pressure monitoring in high-risk pregnant women — a randomised controlled trial” (REMOTE CONTROL trial), a pragmatic non-inferiority unblinded multicentre randomised controlled trial, we aim to determine whether remote BP monitoring in pregnant women at high risk for developing a HDP is as safe as conventional clinic BP monitoring. We will evaluate foetal outcomes as the primary outcome, in addition to maternal outcomes, patient satisfaction and the cost-effectiveness of this strategy. This study protocol follows the SPIRIT reporting guidelines [37].

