### Sample size

The sample size calculation is based on the assumption that the composite foetal outcome will be equal in the remote BP monitoring and control groups: a non-inferiority trial. Prior data indicates that the rate of the composite foetal outcome is approximately 31.1%, drawn from a study previously undertaken in the local high-risk pregnant population [4]. Investigators made a reasoned choice about the acceptable difference in adverse foetal outcome and feasibility of the trial. As a result, the non-inferiority margin was defined as a 15% absolute increase or less in the remote BP monitoring group. With a one-sided α of 0.05, the study will achieve a power of 0.80 if 118 women will be included in each trial arm. Furthermore allowing for a 20% attrition rate, 260 participants will be needed in total, 130 participants in each arm.

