## Discussion

The REMOTE CONTROL trial will be the first non-inferiority randomised controlled trial, powered to evaluate maternal and foetal outcomes conducted within the Australian healthcare system. A composite foetal events outcome was chosen as the primary outcome, as this represents a definitive end-point relevant to clinicians, patients and the healthcare system. If foetal and secondary outcomes from this study are similar with the institution of remote monitoring, there are major potential benefits to patients and the healthcare system. Through reducing the travel costs, clinic visits and waiting times, it is likely to lead to improved compliance for all patients. In addition, it could improve delivery of care to vulnerable populations in rural and remote communities in Australia, which has unique geographic and social considerations.

The trial is designed to be a pragmatic non-inferiority randomised controlled trial. The underlying pathophysiology of HDP is not going to be altered by the proposed intervention, and therefore a non-inferiority trial design was opted for.

The participant population will be those deemed to be high risk for developing a hypertensive disorder of pregnancy. It is this group of women who are currently being referred to and monitored in an Obstetric Medicine clinic within our local health district. This leads to additional visits throughout their pregnancy, in addition to routine antenatal care. In this high-risk population, the rate of HDP in a recent study set in South Western Sydney was 33.8%, with the rate of adverse foetal outcomes (intrauterine growth restriction or pre-term delivery) between approximately 15–17% (4). Therefore, the high incidence of HDP and foetal adverse outcomes in this population lends itself to an adequately powered study without requiring overwhelming numbers to detect a difference between the groups.

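### The aim speaks of remote monitoring being 'as safe as' clinic care, but the test can only exclude a 15-point rise in the composite foetal outcome (31.1% to 46.1%)

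*Protocol article*

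**What the plan says.** The opening paragraph of Methods calls the trial a pragmatic non-inferiority trial and gives its aim as to "determine whether remote BP monitoring in pregnant women at high risk for developing a HDP is as safe as conventional clinic BP monitoring". The abstract's Discussion goes on to consequences: "If proven to be as safe as conventional clinic monitoring, major potential benefits include reducing clinic visits". The main Discussion takes a similar step with a different word, resting the expected benefits on this condition: "If foetal and secondary outcomes from this study are similar with the institution of remote monitoring".

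The test is defined under Sample size. The planning assumption is that "the composite foetal outcome will be equal in the remote BP monitoring and control groups: a non-inferiority trial", and the section states that "the rate of the composite foetal outcome is approximately 31.1" per cent. On the limit, "the non-inferiority margin was defined as a 15% absolute increase or less in the remote BP monitoring group". Its basis is given in one sentence: "Investigators made a reasoned choice about the acceptable difference in adverse foetal outcome and feasibility of the trial". The error rate is a one-sided 0.05, with power 0.80 and 118 women per arm.

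Under Data handling, analysis and result reporting, the primary outcome is to be analysed with a log-link binomial model and reported as an adjusted risk ratio with a 95% confidence interval. Reporting is to follow the CONSORT extension for non-inferiority trials. Nothing in the article limits the phrase 'as safe as' to 'not worse by 15 points or more'.

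**The concern.** A non-inferiority result supports one statement: that a rise as large as the margin has been excluded. Shorthand such as 'as safe as' does little damage when the margin is so small that any harm below it would be negligible. Here the margin is about half the control rate, and the composite includes stillbirth and neonatal death. The article gives no clinical argument that harm below 15 points is negligible; it refers to a reasoned choice that also weighed feasibility.

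The wording matters because the article moves from it to fewer clinic visits and to care for rural and remote women. It also says that no individual earlier study was powered for these outcomes. A pass read as equal safety would therefore carry weight that the test cannot bear.

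**Working it through.** **Inputs.** All come from Sample size: control rate pC = 0.311, assumed true difference 0, margin 0.15, one-sided α = 0.05 (z = 1.645), power 0.80 (z = 0.842), n = 118 per arm. The 95% interval (z = 1.96) comes from Data handling, analysis and result reporting.

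**The plan's own figure.** n = (1.645 + 0.842)² × 2 × 0.311 × 0.689 / 0.15² = 6.18 × 0.4286 / 0.0225 ≈ 117.8, rounded up to 118. The stated number per arm reproduces exactly.

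**What the margin means.** 31.1% + 15 points = 46.1%. The risk ratio is 46.1/31.1 = 1.48, and the margin is 15/31.1 = 48% of the control rate. That is one extra affected pregnancy per 1/0.15 = 6.7 women.

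**Chance of declaring non-inferiority when the true rise is d.** The rule is that the upper limit of the risk difference lies below 0.15. Approximately,

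P = Φ[(0.15 − d)/SE − z], with SE = √[pC(1 − pC)/n + pT(1 − pT)/n] and pT = 0.311 + d.

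For d = 0.05: SE = √[(0.2143 + 0.2307)/118] = 0.0614, so 0.10/0.0614 = 1.63.
- One-sided 0.05: Φ(1.63 − 1.645) ≈ 0.49.
- Two-sided 95% interval: Φ(1.63 − 1.96) ≈ 0.37.

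Enumerating both binomial arms exactly, with the same Wald limit, agrees within 1 point:

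| True rise (points) | Remote-arm rate | One-sided 0.05 | Two-sided 95% interval |
|---|---|---|---|
| 0 | 31.1% | 80% | 70% |
| 2.5 | 33.6% | 66% | 54% |
| 5 | 36.1% | 49% | 37% |
| 7.5 | 38.6% | 33% | 23% |
| 10 | 41.1% | 20% | 12.5% |
| 15 | 46.1% | 5% | 2.5% |

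**Sensitivity to the number analysed.** At a true rise of 5 points and one-sided 0.05, the chance is 46% with 104 per arm (130 less 20%) and 53% with all 130.

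**Effect of the choice of interval on a single result.** Take 42/118 against 37/118, a difference of 4.2 points with SE 6.14 points. The one-sided 95% limit is 4.2 + 1.645 × 6.14 = 14.3 points, which passes. The two-sided 95% limit is 4.2 + 1.96 × 6.14 = 16.3 points, which fails.

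**The case against.** The protocol does not hide its design. The sentence that contains 'as safe as' also says non-inferiority, Sample size states the margin openly, and the article commits to the CONSORT non-inferiority extension. The sentences in both discussions are conditional. Every non-inferiority trial passes some of the time when the true harm lies between zero and its margin. Each component of the composite is also to be assessed separately. All of this stands, and it keeps the point to one about the stated inference and how it is reported.

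It also rules out four stronger readings.

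- A reader might infer that the trial would often pass a harmful strategy without qualification. It would not: at a 15-point rise the error is 5% or 2.5%. The high pass rates belong to true rises well inside the margin.
- A reader might infer that the authors have committed themselves to reporting any pass as equal safety. No sentence says so.
- A reader might take 42/118 against 37/118 as a certain pass. That depends on which interval decides, as shown above.
- The Background gives "an associated high rate of adverse foetal outcomes (intrauterine growth restriction or preterm delivery) between 15 and 17% [4"], and a reader might set the 15-point margin against that rate to get a risk ratio near 2. That rate is for growth restriction or preterm delivery, a different outcome. The composite has its own rate, 31.1%.

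The objection does not remove the gap itself. Stating the margin in one section does not make 'as safe as' a correct description of what a pass would show.

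**Conclusion.** The point holds as one about the claim, not about the calculation. The sample size reproduces and the test controls its error at the margin. What a pass excludes is a rise from 31.1% to 46.1% or more. A true rise of 5 points would pass in 37% to 49% of trials and one of 10 points in 12.5% to 20%, depending on the interval used, so a pass cannot be read as equal safety.

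These figures assume 118 evaluable women per arm, a true control rate of 31.1% and an unadjusted Wald limit on the risk difference. That limit follows the sample-size section. The analysis section gives only an adjusted risk ratio with a 95% interval and states no decision limit on that scale, so the decision rule used here is an assumption. The conclusion is the same under either interval.

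**What to change.** 1. In the abstract's Discussion and the opening of Methods, replace the 'as safe as' wording with: whether an absolute rise of 15 percentage points or more in the composite adverse foetal outcome can be excluded. Align 'similar' in the main Discussion with this.
2. In Data handling, analysis and result reporting, add the risk difference with its confidence interval, judged against the 15-point margin at the stated one-sided 0.05 level (the upper end of a two-sided 90% interval). Keep the adjusted risk ratio alongside it.
3. State that meeting the margin will be reported as the upper limit of the rise that has been excluded, and not as equal safety.

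The cost is one additional analysis on the risk-difference scale, because the planned log-link model yields only risk ratios, and a less favourable headline claim. The margin and the sample size are unchanged, and no additional women are needed.

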### Design and setting

The REMOTE Control trial will recruit patients across 3 metropolitan Australian teaching hospitals; Liverpool, Campbelltown and Bankstown Hospitals. Within these hospitals, women at high risk of developing a hypertensive disorder of pregnancy are referred to specialist obstetric medicine clinics, where their blood pressure is monitored regularly throughout their pregnancy, leading to an additional 6–8 clinic reviews. The non-inferiority trial will compare remote blood pressure monitoring with conventional clinic monitoring in a 1:1 allocation ratio.

The trial has been prospectively registered with the Australian and New Zealand Clinical Trials Registry (ACTRN12620001049965p) in October 2020. Ethics approval was granted by the South Western Sydney Local Health District human research ethics committee (SWSLHD HREC) in June 2021.

### Study population

The study population will be all pregnant women at high risk for developing a hypertensive disorder of pregnancy, that attend the hospital sites for antenatal care. Eligible women must be ≥ 18 years old with at least one of the following high risk features: (1) chronic hypertension; (2) autoimmune disease; (3) pre-existing diabetes mellitus; (4) chronic kidney disease; (5) previous hypertensive disorder of pregnancy; (6) diagnosed with gestational hypertension; (7) IVF pregnancy; or (8) women whose risk of developing early-onset preeclampsia on first-trimester screening is reported to be < 1:100 [38]. Exclusion criteria for participation in the study are (1) evidence of preeclampsia on initial evaluation; (2) inability to access or use a smartphone as assessed by the research midwife on screening and consent; (3) inability to consent or (4) insufficient knowledge of English or other language supported by the application; (5) multiple pregnancy; and (6) lethal foetal abnormalities. The full inclusion criteria, exclusion criteria and definitions are listed in Table 1.

**Table 1 Tab1:** REMOTE CONTROL trial inclusion and exclusion criteria

	**Definition**
**Inclusion criteria**	
Age ≥ 18 years	
Able to provide informed consent	
Able and willing to follow instructions for use of automated BP machine and app-based system	
Chronic kidney disease	Abnormalities of kidney structure or function (either reduced GFR < 90 ml/min/1.73 m^2^, albuminuria or proteinuria) present prior to pregnancy
Autoimmune disorder	Diagnosis of an autoimmune condition such as systematic lupus erythematosus prior to pregnancy
Type 1 or type 2 diabetes mellitus	
Chronic hypertension	Systolic BP > 140 mmHg or diastolic BP > 90 mmHg on at least 2 occasions prior to 20 weeks’ gestation
Previous pregnancy complicated by HDP or diagnosis of gestational hypertension this pregnancy	Previous HDP includes chronic hypertension, gestational hypertension, preeclampsia, or preeclampsia superimposed on chronic hypertension Gestational hypertension (Systolic BP > 140 mmHg or diastolic BP > 90 mmHg on at least 2 occasions after 20 weeks’ gestation)
Confirmation of viable intrauterine pregnancy on dating scan	
IVF pregnancy	
High-risk for developing preeclampsia on first-trimester screening	Reported risk of < 1:100 of developing preeclampsia on commercially available combined first-trimester screening tests
Before 28 weeks gestation	

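### The first-trimester screening criterion is written as a risk below 1:100, contradicting its own high-risk label, and the text and Table 1 apply it to different outcomes

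*Protocol article*

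**What the plan says.** The Study population section describes its target group as follows: "The study population will be all pregnant women at high risk for developing a hypertensive disorder of pregnancy". A woman qualifies if she is an adult "with at least one of the following high risk features", and eight features follow. The eighth is "women whose risk of developing early-onset preeclampsia on first-trimester screening is reported to be < 1:100".

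Table 1 gives the criterion again. Its row is labelled "High-risk for developing preeclampsia on first-trimester screening", and the definition beside that label is "Reported risk of < 1:100 of developing preeclampsia on commercially available combined first-trimester screening tests".

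The Sample size section takes a composite foetal event rate of 31.1% from a study in the local high-risk population. On the margin it says "the non-inferiority margin was defined as a 15% absolute increase or less in the remote BP monitoring group".

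**The concern.** A risk reported as 1:k is the probability 1/k, so a risk below 1:100 is a probability below 1%. A row labelled high-risk is therefore defined by an inequality that only low reported risks satisfy. The same sign stands in both places, and neither corrects the other.

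The two places also name different outcomes. Early-onset preeclampsia is a subset of preeclampsia, so one woman can have two different reported risks. A threshold means little until the risk it applies to is named.

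This is an operative entry rule, and it can admit a woman on its own. It is applied at three hospitals, with recruitment through general antenatal clinics as well as specialist obstetric medicine clinics. Misapplication would not unbalance the arms, because eligibility is settled before randomisation and centre is a minimisation variable. The risk is to the population studied. Women with fewer events, and with little to lose from a change in monitoring, would make a fixed absolute non-inferiority margin easier to meet.

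**Working it through.** **1. What the inequality selects.** Convert each reported risk to 1/k and compare it with 1/100 = 0.0100.

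| Reported risk | Probability | Meets the rule as written (risk below 1:100) | Meets the shorthand reading (1 in fewer than 100) |
|---|---|---|---|
| 1:10 | 0.1000 | no | yes |
| 1:50 | 0.0200 | no | yes |
| 1:99 | 0.0101 | no | yes |
| 1:100 | 0.0100 | no | no |
| 1:101 | 0.0099 | yes | no |
| 1:500 | 0.0020 | yes | no |
| 1:1000 | 0.0010 | yes | no |

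The two readings select opposite groups. Only the shorthand reading fits the row label. Neither admits a risk of exactly 1:100, and the article does not say whether that is intended.

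**2. Whether the article signals the shorthand reading.** It does not. Elsewhere the less-than sign has its ordinary numerical meaning: the GFR limit of 90 in the same table, and the blood pressure target of 140/90 mmHg in Table 3. The cut-off is not stated in the opposite direction anywhere.

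**3. Text against table on the outcome.** The Study population section uses early-onset preeclampsia; Table 1 uses preeclampsia. Nothing says which takes precedence. This ambiguity remains even if the sign is read as intended.

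**4. The plan's own sample size.** Inputs from the Sample size section: p = 0.311 in both arms, margin d = 0.15, one-sided alpha 0.05, power 0.80.

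n per arm = (1.645 + 0.842)² × 2p(1 − p) / d² = 6.18 × 0.4286 / 0.0225 ≈ 117.8, which rounds up to 118.

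This agrees with the plan: "With a one-sided α of 0.05, the study will achieve a power of 0.80 if 118 women will be included in each trial arm". The screening criterion does not enter the calculation.

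**5. Direction of the effect if the event rate fell.** With the same formula and the same 15-point margin:

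| Event rate | n per arm for 80% power | Margin ÷ event rate |
|---|---|---|
| 31.1% | 118 | 0.48 |
| 25% | 104 | 0.60 |
| 20% | 88 | 0.75 |
| 15% | 71 | 1.00 |

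A lower rate makes the margin easier to meet with a given number of women, and larger relative to the risk it is meant to protect. The rates below 31.1% are illustrative, not forecasts.

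**6. Why no size can be given.** Suppose a share w of entrants were low-risk women with event rate q and no excess under remote monitoring. The overall rate would be (1 − w) × 31.1% + w × q, and a true excess D in the other women would appear as (1 − w) × D. The article gives neither w nor q, and does not say whether such women would have an excess. Assumed values, for illustration only:

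- w = 0: the rate stays at 31.1%, and a 15-point excess stays at 15 points.
- w = 10%, q = 12%: 0.9 × 31.1 + 0.1 × 12 = 29.2%; 0.9 × 15 = 13.5 points.
- w = 20%, q = 12%: 0.8 × 31.1 + 0.2 × 12 = 27.3%; 0.8 × 15 = 12 points.

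If q were close to 31.1%, the overall rate would hardly move. That is possible, because the composite counts events other than those caused by preeclampsia. The results only restate what is assumed.

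**The case against.** The strongest reply is that this is a slip of notation with an obvious meaning. The row label, the heading over the list of features and the stated population all point to 1 in fewer than 100. A midwife or physician would have to enrol a woman reported at, say, 1:1000 under a row labelled high-risk, and nothing in the article suggests that this happens. Much of this stands: the intent is fairly clear, and nobody appears to have chosen to recruit low-risk women.

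A reader might infer that women at 1:50 are shut out. The article does not support that in general. The feature is one of eight and is not an exclusion criterion, so even on the literal reading a woman at 1:50 who has another listed feature still enters. Only women whose sole feature is the screening result would be missed.

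The mismatch between early-onset and any preeclampsia can be called a one-word difference in a condensed article. It is small, but clear intent about the sign does not resolve it. Both places state an outcome, and the outcomes differ.

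**Conclusion.** The criterion is wrong as written, in two respects. Its inequality contradicts its label in both places where it appears, and those two places attach it to different outcomes. Neither statement depends on an assumption.

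The consequences are conditional. If sites apply the rule literally, or differently from one another, low-risk women could enter and some screen-positive women could be missed. The event rate would then probably fall below 31.1%, and a true excess could be diluted against the 15-point margin. The amount cannot be quantified from the article.

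A reader might go further and conclude that the trial selects low-risk women and is biased toward non-inferiority. The article does not support that: it gives no sign that the sign is being applied against the label, and no figure for the share of women who enter by this route. The sample size of 118 per arm stands. This is a real defect in an entry rule, cheap to correct, whose intent is probably recoverable.

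**What to change.** - Reconcile the Study population section and Table 1 so that the direction of the inequality agrees with the high-risk label. Writing it as a probability, or in words, would remove the ambiguity.
- State whether a reported risk of exactly 1:100 qualifies. The article leaves this open, and it is for the investigators to settle.
- Name the same outcome in both places, so that it is clear which reported risk is compared with the threshold.
- Recruitment began in July 2022, so list the women enrolled on this criterion alone, confirm each one's eligibility against the clarified wording, and report how many there were. That count would also show whether dilution is a practical concern.

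The cost is a wording amendment submitted to the ethics committee and a short record check at three sites. The sample size does not change.
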